**Figure 3 BMJOPEN2016011330F3:**
[figure not shown]
Covariates and comorbidities to be obtained from EHR. COPD, chronic obstructive pulmonary disease; CPRD, Clinical Practice Research Datalink; EHR, electronic health record.

### Activity algorithms

Time-location-activity patterns of individuals are an important determinant of personal exposure to air pollution. In this study, we will derive activity pattern combining personal sensing technology with machine learning computational techniques for automated classification and without recourse to manual activity diaries. This method is currently being validated by the University of Cambridge in a pilot cohort of 45 healthy volunteers over a week as they go about their daily lives, each of whom will keep a detailed smartphone-based activity diary. The automated classification of exposure events will provide improved estimation of personal exposure and dose which will be used to draw associations with subjective symptoms (diary cards), measured outcomes (peak flow and general practice/hospital records from CPRD) and medication use.

### Validation of the London Hybrid Exposure Model

King's College London has previously developed a time-activity exposure model study known as the London Hybrid Exposure Model (LHEM),^23^ but full evaluation against measured data was not possible at the time due to limitations in mobile monitoring technology. The extensive measurement data set gathered will primarily provide a validation data set for the LHEM. The GPS coordinates collected with the PAMs, together with the automated classifications of time-activity models created, will be fed into the model. This will produce a modelled time-series exposure estimate for each pollutant. These estimates will be compared with measured pollutant exposure and performance for targeted pollutants in different microenvironments, with the aim of deriving uncertainty estimates for future model applications. Calibrated model results will be compared with static exposure estimate methodologies, such as central monitor or postcode, to quantify the exposure misclassification associated with each. The integrated data set collected during the monitoring phase will also provide the opportunity to verify and refine model infiltration factors for indoor and transport microenvironments, incorporating emissions from indoor sources and human activities, such as cooking and smoking.

This combined monitoring–modelling methodology for time-activity exposure model development and evaluation will be applicable to a wide range of cohort and epidemiological studies investigating links between environmental exposure and diverse health outcomes.

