### Development of a COPD prediction model

Associations between exacerbations with spatiotemporally resolved environmental exposure established in the Statistical associations between personal exposure with COPD-related health outcomes section will be combined with the time-activity exposure model (LHEM) to create a predictive model for COPD exacerbations across London. First, time-location-activity patterns of the COPD cohort will be compared with general population-level time-activity patterns derived from the Traffic Pollution and Health in London project.^24^ This will be used to test the applicability of general population behaviour patterns when assessing COPD associations in epidemiological studies.

The association between personal exposure to air pollution with COPD exacerbations estimated in the Statistical associations between personal exposure with COPD-related health outcomes section will form the basis of the COPD prediction model. This model will be used to create high resolution (20×20 m grid) daily COPD exacerbation risk maps for the years 2005–2011, based on modelled meteorological and pollutant conditions, coupled with typical patient with COPD time-activity patterns identified in the Activity algorithms section. The model will thus retrospectively predict days and locations more likely to trigger a worsening of symptoms and/or exacerbation in patients with COPD over this time period.

The performance of the predictive model will be evaluated using validated methods for patient identification^21^ from EHRs, CPRD, HES and ONS death data excluding data from the COPE cohort. Spatial and temporal patterns of recorded exacerbations will be compared with model risk estimates linked to the home address. If it is demonstrated that there are significant associations between model predictions and recorded exacerbations, the algorithms used will be generalised for use outside of London. These algorithms will provide an opportunity for the development of a national COPD forecasting service with proven performance in predicting increased risk of exacerbations.

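### The London Hybrid Exposure Model is checked against measured exposure only when fed with participants' own tracks, while the risk maps run it on typical COPD activity patterns

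*Protocol article*

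**What the plan says.** Two sections of the protocol article matter here.

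**Validation of the London Hybrid Exposure Model.** The model inputs are individual: "The GPS coordinates collected with the PAMs, together with the automated classifications of time-activity models created, will be fed into the model". The resulting time series for each pollutant is compared with measured exposure. The section also looks at "performance for targeted pollutants in different microenvironments, with the aim of deriving uncertainty estimates for future model applications". A second comparison is with simpler methods: "Calibrated model results will be compared with static exposure estimate methodologies, such as central monitor or postcode". Its purpose is to quantify the exposure misclassification of each.

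**Development of a COPD prediction model.** The model produces "high resolution (20×20 m grid) daily COPD exacerbation risk maps for the years 2005–2011". These are built from modelled weather and pollution, "coupled with typical patient with COPD time-activity patterns identified in the Activity algorithms section". As a preliminary step, "time-location-activity patterns of the COPD cohort will be compared with general population-level time-activity patterns". The prediction model is then evaluated against "EHRs, CPRD, HES and ONS death data excluding data from the COPE cohort", with risk estimates linked to the home address. Significant associations there are the condition for generalising the algorithms beyond London.

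**The concern.** A time-activity exposure model has two broad sources of error. One is the concentration that it assigns to a place and microenvironment. The other is where it puts the person and what it has the person doing. Supplying the person's own GPS track and classified activity largely removes the second source, apart from classification error. Supplying typical patterns brings it back.

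The article itself treats this source as important. Its Activity algorithms section calls individual time-location-activity patterns an important determinant of exposure, and its Introduction lists the lack of detailed activity patterns among the critical limits of earlier work.

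Two results could therefore be read as properties of the maps when they belong to another mode of the model. The first is the uncertainty estimate. The second is any advantage over postcode or central-monitor exposure. Patients in the historical records outside the cohort carried no monitor, so the mode with individual tracks cannot be run for them. The mode that can be run might be clearly better than postcode exposure or hardly better at all, and the comparisons described would not show which.

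**Working it through.** The article states no figure for exposure error, so there is none to reproduce. The check sets the planned steps side by side and then writes out what the validation step estimates.

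**1. Planned checks and what each one measures**

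| Step | Activity input to LHEM | Compared with | What it measures |
|---|---|---|---|
| Validation, first comparison | Own GPS and classified activity | PAM measurements | Exposure error of the GPS-fed mode |
| Validation, second comparison | Calibrated model; GPS-fed is the only run described | Central monitor, postcode | Misclassification of static methods |
| Prediction model, activity comparison | None (patterns only) | General-population patterns | Difference in behaviour |
| Prediction model, evaluation | Typical COPD patterns | Recorded exacerbations outside the cohort | Association with risk |

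The combination of typical-pattern input and PAM comparison does not occur. The evaluation against records does use the applied mode, but it returns no exposure error. Because no static comparator is named at that step, an association found there would not show whether typical patterns add anything to postcode exposure.

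**2. Decomposition**

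For one participant-day let M be the PAM value, G the LHEM value from the person's own track, and T the LHEM value from typical patterns. Then

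M − T = (M − G) + (G − T)

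Var(M − T) = Var(M − G) + Var(G − T) + 2 Cov(M − G, G − T)

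The planned validation estimates the first term only. The second term is the error from substituting typical for individual patterns. Both could be estimated from data that the cohort will supply.

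**3. Illustration of size (assumed inputs)**

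Let r = SD(G − T) / SD(M − G), and assume zero covariance. Then

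- total SD / validated SD = √(1 + r²)
- true coverage of a nominal 95% interval built on the validated SD = 2Φ(1.96 / √(1 + r²)) − 1, for normal errors.

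| r (assumed) | SD ratio | True coverage |
|---|---|---|
| 0.25 | 1.03 | 94.3% |
| 0.5 | 1.12 | 92.0% |
| 1 | 1.41 | 83.4% |
| 2 | 2.24 | 61.9% |

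Nothing in the documents fixes r. The effect is trivial at the low end and serious at the high end.

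**4. How far the direction is settled**

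With correlation ρ between the two components the ratio becomes √(1 + r² + 2ρr). It exceeds 1 only if ρ > −r/2. At r = 0.5 and ρ = −0.25, for example, 1 + 0.25 − 0.25 = 1 and there is no inflation. Independence is therefore an assumption that bears on the result, and the table is an illustration, not an estimate.

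**The case against.** **Fixing location is sound component validation.** Error by microenvironment, and the refinement of infiltration factors, need known location and activity. This stands, and it is a reason to keep the GPS-fed run. It does not make that run a measure of the applied mode.

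**The applied mode is tested.** A reader might infer that the mode used for the maps is never validated. The article does not support that: the prediction model is to be evaluated against independent recorded exacerbations, and generalisation depends on the result. What remains is narrower, namely that the test concerns risk and not exposure.

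**Understated uncertainty is not shown.** A reader might infer that the maps will carry too small an uncertainty. The article does not say that the validation estimates are attached unchanged to the maps, and it promises no uncertainty figure for them. Its stated aim, "with the aim of deriving uncertainty estimates for future model applications", makes a carry-over natural but not certain. The discrepancy between model and PAM also contains sensor error and activity-classification error, which widen it, so even the net direction is open.

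**The maps are not individual predictions.** They describe days and places of raised risk for typical patients. One person's departure from a typical pattern is then partly spread between persons, not error in the map value. This stands and limits the illustration above, which is at participant-day level. The error has to be summarised at the level at which the maps are read.

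**Two further over-readings.** The article speaks of typical patterns in the plural and gives no number, so it does not describe a single pattern for everyone. The home address is used to link risk estimates in the evaluation; it is not stated as an LHEM input.

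**A condensed article may leave model runs to a fuller document.** This has some force. But the article does specify the validation inputs, the comparators and the purpose, and it specifies a different activity input for the application. The point rests on what it states.

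**Conclusion.** The point holds in a limited form. Exposure-level accuracy and uncertainty are planned only for LHEM runs fed with individual tracks, while the risk maps use typical COPD patterns. The evaluation against recorded exacerbations does not fill that gap. If the uncertainty, or the comparison with static methods, is carried over to the maps, the error from substituting typical patterns is left out.

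Its size cannot be computed from the documents. The SD ratios of 1.03 to 2.24 rest wholly on assumed values of r from 0.25 to 2, on independent and normal errors, and on a participant-day interpretation.

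The associations estimated in the cohort are not affected. The matter concerns what can be claimed for the accuracy of the mapping model and for its gain over simpler exposure methods. An inexpensive addition to the validation step would settle it.

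**What to change.** In the section on validation of the LHEM, add a second run for every participant-day:

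1. Keep the run fed with the participant's own GPS and classified activity. Report it as validation of the concentration and microenvironment components.
2. Add a run fed with the typical COPD pattern or patterns, anchored at the participant's home location and built without that participant's data.
3. Compare the second run with the PAM measurements, and set its error beside those of the central-monitor and postcode estimates on the same participant-days.
4. Use the error of the second run when stating uncertainty for the 2005–2011 maps, summarised at the level at which the maps are interpreted (for example, averaged over patients for a day and area if the maps are not meant for individuals).

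No new data are needed. The cost is the extra model runs, including rebuilding the typical patterns with each participant left out, and a reported accuracy that may look less favourable. In return the study can say whether the mode that can be applied outside the cohort improves on postcode or central-monitor exposure.

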## Abstract

**Introduction:**

Relationships between exacerbations of chronic obstructive pulmonary disease (COPD) and environmental factors such as temperature, humidity and air pollution are not well characterised, due in part to oversimplification in the assignment of exposure estimates to individuals and populations. New developments in miniature environmental sensors mean that patients can now carry a personal air quality monitor for long periods of time as they go about their daily lives. This creates the potential for capturing a direct link between individual activities, environmental exposures and the health of patients with COPD. Direct associations then have the potential to be scaled up to population levels and tested using advanced human exposure models linked to electronic health records.

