### Statistical associations between personal exposure with COPD-related health outcomes

The monitoring phase of the project will create a unique high resolution multiparameter data set of individual exposure patterns over an extended period. These data will be mined to explore associations between participant's health (symptoms, lung function and exacerbations) and the environment through (1) direct measurements, (2) derived variables and (3) modelled outputs. Explanatory variables will include peak, mean and cumulative exposure, rate of change, activity level and pollutant dose/intake, lag effects, ambient pollution or temperature episode effects, pollutant source types (eg, traffic, regional, domestic) and indoor/outdoor ratios. The aim will be to identify and explain any observed associations, allowing the translation of results into healthcare relevant information and possible policy updates.

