### Statistical analysis

Survival analyses for repeated measurements will be performed on the basis of the Cox proportional hazards model. Interval censoring for handing ties over appropriate event time intervals will be applied specifying each participant to a stratum. Essentially, conditional regression will be used to estimate the HR of subjective health symptoms and exacerbations in relation to seasonal variations of personal exposure (prognostic factor). The conditional regression models will be developed by the PHREG procedure in SAS V.9.3 (North Carolina, USA) with robust sandwich covariance for aggregated data. Ties will be handled with the DISCRETE method. Medication use will be inserted as a control factor in the models.

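### The LHEM prediction model may be generalised on a significance test alone, with no simpler-exposure benchmark, so the stated rule cannot show that dynamic exposure improves COPD associations or prediction

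*Protocol article*

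**What the plan says.** The Abstract says the relation between exacerbations and the environment is poorly characterised "due in part to oversimplification in the assignment of exposure estimates to individuals and populations". The Introduction develops this. It cites reviews in which pollutants had modest but statistically significant effects on COPD admissions and mortality, calls that evidence only indicative, and lists among the weaknesses of most such studies their dependence on a few fixed monitoring sites. The Discussion presents the finer detail of assessment as the strength of this study.

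Three later sections bear on whether finer exposure helps:

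- **Validation of the London Hybrid Exposure Model.** Calibrated LHEM results are to be "compared with static exposure estimate methodologies, such as central monitor or postcode, to quantify the exposure misclassification associated with each".
- **Statistical associations, and Statistical analysis.** Health outcomes are related to exposure through "1) direct measurements, (2) derived variables and (3) modelled outputs", and the explanatory variables include "lag effects, ambient pollution or temperature episode effects". The Cox model uses personal exposure as the prognostic factor, and interval censoring for ties "will be applied specifying each participant to a stratum".
- **Development of a COPD prediction model.** The association found in the cohort "will form the basis of the COPD prediction model", combined with the LHEM and typical COPD time-activity patterns, to give risk maps for 2005–2011. For evaluation in records outside the cohort, "Spatial and temporal patterns of recorded exacerbations will be compared with model risk estimates linked to the home address". If the association is significant, the algorithms are to be generalised beyond London.

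**The concern.** The plan fixes a success rule that does not match its rationale. A significant association between LHEM-based predictions and exacerbations shows that the predictions carry some signal. It does not show that they carry more than a central monitor or a postcode concentration would. The article's own account is that earlier work, mostly with coarse exposure, already reached significance.

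The one planned comparison with static methods stops at exposure values. How far a static method departs from measured or modelled exposure does not by itself say how much the health association or the prediction suffers. In a participant-stratified model, only part of that departure matters.

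At stake is what may be concluded about detailed exposure, and the case for a national forecasting service, which the article describes as having proven performance. The cohort associations themselves are not invalidated.

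**Working it through.** **1. Which methods are compared, and on what**

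| Section | Exposure methods | Compared on |
|---|---|---|
| Validation of the LHEM | LHEM against measured exposure; LHEM against central monitor or postcode | Exposure values |
| Statistical associations; Statistical analysis | Measured, derived, modelled; ambient episodes as explanatory variables | Association with health; no comparison between methods stated |
| Development of a COPD prediction model | LHEM-based model only | Significance of association with recorded exacerbations |

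No row sets a static and a detailed exposure side by side against a health outcome. In the last row, the use of typical activity patterns and the home address also removes some of the person-specific movement that separates the LHEM from a postcode method, so a benchmark is especially informative there.

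**2. The plan's own power figure**

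Inputs (Recruitment of panel participants): 200 exacerbations, p<0.05 (two-sided assumed), 80% power, RR 1.65 in the highest 20% of days. Schoenfeld: events = (1.960 + 0.842)² / [q(1−q)(ln RR)²].

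- q = 0.20, RR 1.65: 7.849 / (0.16 × 0.2508) = 196 events. With 200 events, power is 80.9%.
- q = 0.10, RR 2.00: 7.849 / (0.09 × 0.4805) = 182 events, so the stated 2.00 is slightly conservative.

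The figure reproduces, and the power statement is not at fault.

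**3. What a significance rule can separate**

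Assume a static metric with within-person correlation ρ with personal exposure (bivariate normal, non-differential; ρ is not in the article). Let v be the chance that a day in the static top 20% is in the true top 20%, and f = 0.2(1−v)/0.8 the same chance for the other days. Then observed RR = (1 + 0.65v)/(1 + 0.65f). For ρ = 0.7, v ≈ 0.565 and f ≈ 0.109, giving 1.367/1.071 = 1.277.

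| ρ | Observed RR | Power at 200 events | Events for 80% power |
|---|---|---|---|
| 1 | 1.650 | 81% | 196 |
| 0.9 | 1.429 | 52% | 385 |
| 0.8 | 1.342 | 38% | 567 |
| 0.7 | 1.277 | 28% | 823 |
| 0.5 | 1.175 | 15% | 1,878 |
| 0.3 | 1.096 | 7.5% | 5,862 |

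With enough records, every row is likely to pass a significance test. The number of external exacerbations is not given. Passing therefore does not distinguish a good exposure method from a poor one; the size of the effect or of the predictive gain does.

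**4. Which part of the misclassification matters**

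With each participant as a stratum, an error that is constant for a person cancels. Take true exposure b + t + w with variances 1 (person), 1 (day) and 0.25 (all assumed). A central-monitor metric is t. A postcode-type metric is b + 0.3t + noise of variance 0.25.

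- Overall correlation: central 1/√2.25 = 0.67; postcode 1.3/√(2.25 × 1.34) = 0.75.
- Within-person correlation: central 1/√1.25 = 0.89; postcode 0.3/√(1.25 × 0.34) = 0.46.

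A simulated data set of 160 people and 180 days gave 0.68 and 0.72 overall, and 0.88 and 0.43 within person. The overall ranking reverses the ranking that the stratified model uses. Likewise, with within-person r = 0.7 and unseen between-person variance k times the within-person variance, pooled R² = 0.49/(1+k) = 0.245, 0.163 and 0.098 for k = 1, 2 and 4, against 0.49 within person.

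**5. Precision of a cohort comparison**

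For ρ = 0.7, the two top-20% indicators correlate (0.2 × 0.565 − 0.04)/0.16 = 0.456. Each log RR has variance 1/(200 × 0.16) = 1/32. The variance of the difference is 2 × (1/32) × (1 − 0.456) = 0.034, so SE = 0.184. The difference is ln 1.65 − ln 1.277 = 0.256, or 1.39 SE, giving power Φ(1.39 − 1.96) ≈ 28%. Exacerbations alone would give an imprecise comparison.

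**The case against.** The strongest defence is that the article condenses a fuller plan. Its fourth stage is validation of an exposure model, no stage promises a test of whether finer exposure improves health results, and refitting models with other exposures is often left to an analysis plan. The validation section does what it says. This stands as far as the missing refit goes. It does not cover the generalisation rule, which the article states itself and which has no comparator.

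A reader might infer more than the documents support:

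- *That the study is unable to compare the methods.* It is not. Static estimates are planned for the cohort, and the data would allow them in the same models. Modelled outputs and ambient episodes already enter the health analysis. The limit lies in the comparison and rule as written.
- *That a static method with large misclassification would give nearly the same association*, because Berkson-type error causes little bias. That argument suits a linear, continuous exposure. The article powers on the highest 20% or 10% of days, where ρ = 0.7 would turn 1.65 into 1.28.
- *That reported misclassification will understate the useful signal 2- to 5-fold.* This assumes a pooled R² that the article never names. Its modelled time series and results by microenvironment are compatible with within-person reporting.

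Two practical objections also stand. A postcode value that is constant over time cannot be estimated in a participant-stratified model, and about 200 exacerbations give little power to separate methods. Both shape the remedy.

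**Conclusion.** The point holds as a badly fixed success criterion and a static comparison that stops short of the health model. As written, a positive result would show that LHEM-based predictions are associated with exacerbations, not that they improve on simpler exposure, which is the study's rationale. This follows from the article's own text and needs no assumed values.

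The size of the gain is unknown and could be small or large: the attenuated RRs run from 1.43 to 1.10 over ρ = 0.9 to 0.3. All correlations, variance components and R² figures above are illustrations under assumed values, and they establish only that the consequence for health results has to be measured. The change is worth making. It affects what can be claimed for the dynamic model, not the validity of the planned associations.

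**What to change.** 1. **Prediction model.** Run the same evaluation on the same external records with a static-exposure model (daily central-monitor or daily postcode concentration, plus season and temperature). Base any claim of benefit, and the decision to generalise, on the gain in predictive performance with its confidence interval, not on significance alone.
2. **Cohort models.** Refit the participant-stratified models on the same participant-days with PAM, LHEM and time-varying static exposures in turn, omitting any static metric that is constant within a person. Report effect estimates and model fit with participant-bootstrap confidence intervals. Include peak flow, which the article expects to have more power, because differences for exacerbations will be imprecise.
3. **LHEM validation.** Report misclassification separately for its within-person and between-person parts, since only the first enters a participant-stratified model.

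The cohort parts cost analysis time, since static estimates are already planned there. The prediction benchmark costs more: the evaluation excludes the cohort, so static estimates must be built for the 2005–2011 external records. The advantage claimed for the LHEM may also turn out smaller.
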